### 3.9. Statistical Analysis

All analyses will be conducted according to the intention-to-treat (ITT) principle, including all randomized participants in the groups to which they were originally allocated, regardless of adherence to the intervention, thereby ensuring that the primary effectiveness analysis remains fully powered even if a significant proportion of participants fail to meet compliance thresholds. A secondary per-protocol analysis may be conducted including participants who complete the post-intervention assessment and, in the intervention arms, meet the predefined adherence criteria (≥70% attendance). In the event that a large majority of participants fail to reach this updated 70% attendance threshold due to severe treatment-related toxicity, a secondary sensitivity dose–response analysis will be implemented, modeling session attendance as a continuous covariate to evaluate the threshold-independent impact of intervention volume on neurocognitive outcomes.

Descriptive statistics will be used to summarize baseline sociodemographic and clinical characteristics by study arm. Continuous variables will be presented as means and standard deviations or medians and interquartile ranges, depending on their distribution. Categorical variables will be presented as frequencies and percentages. Baseline comparability between groups will be described, but statistical testing of baseline differences will not be used to determine participant inclusion or exclusion from the analysis.

The primary effectiveness analysis will evaluate change in Montreal Cognitive Assessment (MoCA) total score from baseline (T0) to post-intervention assessment (T1). Linear mixed models (LMM) will be constructed using a Restricted Maximum Likelihood (REML) estimation approach. The model will include fixed effects for group, time, and the Group × Time interaction term, and a parsimonious random-effects structure restricted to a random intercept for each participant to account for within-subject correlation across time while excluding random slopes. The Group × Time interaction will be the main parameter of interest. Both unadjusted and adjusted models will be calculated to verify the robustness of the intervention effect.

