The planned between-group comparisons for the primary outcome will focus on the ALMA group intervention (G2). The first planned comparison will evaluate the difference in change in MoCA total score from T0 to T1 between G2 and the health education control group (G0). The second planned comparison will evaluate the difference in change in MoCA total score from T0 to T1 between G2 and the individual cognitive training group (G1), in order to assess the potential added value of the multidimensional group-based ALMA intervention over individual cognitive training. The comparison between G1 and G0 will not be considered a planned efficacy comparison and, if reported, will be interpreted as exploratory.

To strictly prevent statistical overfitting and safeguard the degrees of freedom given the target sample size of 21 participants per study arm, the adjusted model will be parsimoniously restricted. Specifically, a maximum of two pre-specified baseline covariates will be simultaneously controlled for as fixed effects: chronological age (in years) and educational level (in years of formal schooling). Baseline cognitive stratification variables will be excluded from the model as covariates, given that their equilibrium across groups is already mathematically guaranteed by the stratified block randomization procedure (Section 2.5). Additional clinical and psychological variables including disease stage, treatment modality, time since diagnosis, cancer-related fatigue/performance status, baseline anxiety symptoms (Hamilton Anxiety Scale), and baseline ECOG Performance Status will be exclusively examined in exploratory or sensitivity analyses rather than included simultaneously in the primary adjusted model.

Because two planned comparisons will be conducted for the primary outcome, namely G2 versus G0 and G2 versus G1, Holm–Bonferroni correction will be applied to these two comparisons to control the family-wise error rate. Holm–Bonferroni correction will also be applied to secondary outcome comparisons within each outcome family when appropriate. Any additional post hoc analyses, including G1 versus G0 comparisons, will be clearly labelled as exploratory.

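### The adjusted mixed model adds age and education only as time-constant main effects, so it cannot check robustness of the Group × Time estimate, and baseline MoCA is not used as a predictor

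*Protocol article*

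**What the plan says.** Section 3.9 fixes the primary analysis as a REML mixed model: "The model will include fixed effects for group, time, and the Group × Time interaction term", with "a parsimonious random-effects structure restricted to a random intercept for each participant". It adds that "The Group × Time interaction will be the main parameter of interest". Sections 3.1 and 3.2 give two assessments, T0 and T1, and define the endpoint as the between-group difference in T1 − T0 change.

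On adjustment, section 3.9 states that "Both unadjusted and adjusted models will be calculated to verify the robustness of the intervention effect". In the adjusted model, "a maximum of two pre-specified baseline covariates will be simultaneously controlled for as fixed effects"; the two are age and years of schooling. No covariate × time term is mentioned. It also states that "Baseline cognitive stratification variables will be excluded from the model as covariates", on the ground that stratified randomization already guarantees their balance.

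Section 4.1, in its paragraph on mitigation, instead lists the baseline MoCA stratum beside age and education among the prespecified covariates, and presents this adjustment as a response to possible bias. Nowhere does continuous T0 MoCA enter as a covariate, and nowhere are the arms given a common T0 mean. Section 3.9 applies the same framework to every secondary outcome.

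**The concern.** In a two-visit model with free group means at T0, the Group × Time coefficient is the difference in mean change. A covariate that does not vary over time and enters only as a main effect shifts a woman's T0 and T1 values by the same amount, so it drops out of her change. The adjusted model then returns the unadjusted answer whatever the data are. A chance imbalance in age or education that really affected change would go uncorrected, and the agreement could still be taken as evidence of robustness.

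There is also a precision question. T0 MoCA is measured on every woman before randomization, but it serves only as the first response value. Balance across arms is not a reason to leave it out. Adjusting for a prognostic baseline removes outcome variance even under perfect balance, and balance on <26 versus ≥26 leaves variation within each stratum. When randomization is stratified on a prognostic factor that the model ignores, the model's standard error is too large.

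**Working it through.** **Inputs.** Two visits, random intercept, 21 women per arm (19 after attrition), about 10% attrition, Holm's first step at 0.05/2 = 0.025, effect 2.95 and SD 3.48 (sections 2.4, 3.1 and 3.9). Section 2.4's effect size reproduces: 2.95/3.48 = 0.848 ≈ 0.85. It does not say whether 3.48 is the SD of the score or of the change. The only correlation given is the test–retest r = 0.92 (section 3.2). The four-month correlation ρ under treatment is not stated, so ρ = 0.6–0.8 is an assumption.

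**1. Algebra, complete data.** Write each woman's data as D = T1 − T0 and S = T1 + T0. Under a random intercept with equal residual variance, D and S are independent.
- E[D] = time + (Group × Time) for her arm. The age and education terms cancel.
- E[S] contains age, education and a free group term. Because the group term is free, S carries no information on Group × Time.

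The estimate is therefore the difference in mean D, and its SE comes from the spread of D. Both are unaffected by age and education.

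**2. Numerical check.** REML random-intercept fits, 21 per arm, SD 3.48, ρ = 0.6, 200 simulated trials per scenario:

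| Scenario | Adjusted − unadjusted estimate |
|---|---|
| Complete data, age + education | at most 2e-13 |
| Complete data, MoCA stratum added as main effect | at most 3e-13 |
| 10% missing T1, age + education | mean 0.04–0.05, at most 0.25 (SE about 1.0) |
| 15% missing T1, age + education | mean 0.06, at most 0.29 |
| Complete data, age and education × time | up to 0.59 |

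With complete data the mixed model also equals least squares on change scores (SE 0.953 for both). The estimate moves materially only when covariates may act on change. Adding the stratum as a main effect, as section 4.1 suggests, repairs nothing.

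**3. Baseline adjustment: SE reported by the model.** With score SD σ at both visits, the per-woman variance is 2σ²(1 − ρ) for change and σ²(1 − ρ²) after adjusting for T0. The ratio is (1 + ρ)/2, and the SE falls by 1 − √[(1 + ρ)/2].

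| ρ | variance ratio | SE reduction |
|---|---|---|
| 0.6 (assumed) | 0.80 | 10.6% |
| 0.7 (assumed) | 0.85 | 7.8% |
| 0.8 (assumed) | 0.90 | 5.1% |
| 0.92 (section 3.2) | 0.96 | 2.0% |

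The simulation at ρ = 0.6 agrees: mean SE 0.857 against 0.953, a ratio of 0.90.

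**4. Baseline adjustment: true sampling variance.** Section 2.5 stratifies on MoCA <26 versus ≥26, which already limits T0 imbalance. Simulations used 63 women in four strata with blocks of 3 and 6, assuming that the MoCA cut falls at the median and that treatment modality splits evenly. The ratio of sampling variances (baseline-adjusted to change score) was about 0.92–0.93, 0.94, 0.96 and 0.99–1.00 at ρ = 0.6, 0.7, 0.8 and 0.92. The change-score model's SE exceeded its true sampling SD by roughly 7% at ρ = 0.6, falling to about 2% at 0.92. The adjusted model's SE was close to correct.

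**5. Nominal power, both readings of 3.48.** G2 versus G0, 19 per arm, two-sided 0.025, noncentral t with 54 df (change) or 53 df (adjusted), using the ratios in step 3:

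| ρ | 3.48 = SD of change | 3.48 = SD of score |
|---|---|---|
| 0.6 | 62% → 73% | 73% → 83% |
| 0.7 | 62% → 70% | 85% → 91% |
| 0.8 | 62% → 67% | 96% → 98% |
| 0.92 | 62% → 64% | about 100% for both |

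Holding the SD of change at 3.48 implies a score SD of 3.48/√[2(1 − ρ)] = 3.9, 4.5, 5.5 and 8.7 down the rows. The last is implausible on a 0–30 scale.

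**The case against.** The strongest case for the plan is that its primary analysis is valid. The endpoint is defined as a difference in change, and the model estimates that without bias under randomization and retains incomplete pairs under missing at random. Preferring a baseline-adjusted model is a matter of efficiency. All of that stands. A reader might infer that the primary estimate is biased or invalid; the documents do not support that.

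Exact equality also holds only with complete pairs. At the planned attrition the two estimates differ slightly, and age and education may make the missing-at-random assumption more plausible. So it would be too strong to say that the adjusted model can never differ. But the shift is about 5% of a standard error on average and comes through the incomplete pairs, so it is not a check on covariate imbalance in change.

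An article may leave interactions with time to an analysis plan that is not shown. Entry as fixed effects does not strictly exclude them, but main effects is the natural reading of the text.

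On size, a reader might take the 62% to 73% row as the gain. It needs an assumed ρ of 0.6 and one of two readings of 3.48. Likewise (1 + ρ)/2 is not the reduction in true sampling variance, because stratification already supplies much of that. What remains is mainly that the present standard error is too large.

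Finally, the two-covariate cap guards against overfitting, so any remedy has to deal with it. A linear baseline term would not remove the MoCA ceiling that section 6 already acknowledges.

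**Conclusion.** The point holds for the model as written. With complete data the adjusted and unadjusted Group × Time results are identical by construction. With about 10% missing T1 they are nearly so (about 0.05 points on average). Their agreement cannot verify robustness. This does not depend on ρ or on the SD; it rests on age and education entering as main effects only.

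The loss of precision is real in direction but modest and uncertain in size. The reported SE would fall by about 2% at r = 0.92 and by about 5–11% at assumed ρ of 0.8–0.6. Sampling variance would fall by roughly 0–8%, given the stratification assumptions above. Power gains should be shown under both readings of 3.48 or left out.

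Sections 3.9 and 4.1 also contradict each other on whether the baseline MoCA stratum is a covariate. Neither version makes the check informative if the stratum enters as a main effect. This should be corrected, but it does not invalidate the primary comparison.

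**What to change.** 1. Make the primary model baseline-adjusted. Either use ANCOVA of T1 MoCA on arm and continuous T0 MoCA, with the treatment-modality stratum, or keep the mixed model with a T0 mean common to all arms (a constrained longitudinal model). The second retains incomplete pairs and so fits the existing missing-data approach better.
2. If age and education stay in a robustness model, enter them as covariate × time terms in the mixed model or as covariates in the ANCOVA.
3. Restate the two-covariate cap so that it is clear whether T0 MoCA and the stratification factor count towards it. Drop balance from stratification as the reason for omitting baseline MoCA.
4. Reconcile sections 3.9 and 4.1 on the MoCA stratum.
5. Use the same form for the secondary outcomes.

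The cost is analysis wording. No new data are needed, and the target remains the between-arm difference in change. The baseline adjustment adds one or two parameters to the primary model and an assumption that T1 is linear in T0.

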### 2.5. Randomization and Allocation Concealment

To ensure numerical balance and a homogeneous distribution of prognostic factors across the three study arms, a stratified block randomization method will be employed. Randomization will be stratified based on two baseline prognostic variables: (1) baseline cognitive status, categorized according to the Montreal Cognitive Assessment score (MoCA < 26 vs. ≥26), and (2) oncological treatment modality, classified according to its systemic neurotoxic potential: systemic chemotherapy with or without radiotherapy versus endocrine/hormone therapy or localized radiotherapy alone.

Following stratification, participants will be randomly assigned to one of the three study arms using randomly varied blocks of size 3 and 6. The random allocation sequence will be generated before the start of recruitment by an independent researcher using Epidat 4.2 software. This researcher will not be involved in participant recruitment, eligibility assessment, baseline or post-intervention outcome assessment, intervention delivery, data management, or statistical analysis.

The random allocation sequence will be stored in a password-protected file and will remain inaccessible to the Principal Investigator, oncology team, intervention providers, outcome assessors, and statistician until eligibility has been confirmed, written informed consent has been obtained, and all baseline assessment procedures (T0) have been completed.

After completion of T0, the Principal Investigator will access the next available allocation within the corresponding stratified stratum and assign the participant to the allocated study arm. The assigned group will then be communicated to the intervention coordinator. The allocation will be recorded in a secure allocation log maintained separately from the assessment database.

This procedure will ensure that group allocation cannot influence eligibility confirmation, informed consent, or baseline assessment. Because the Principal Investigator will become aware of group allocation after T0, this trial will be conducted as an open-label study, and this limitation will be addressed through standardized assessment procedures and blinded statistical analysis using neutral group labels.

The three study arms are defined as follows:G0 (Control Group): Health Education Programme.G1 (Active Comparison): Cognitive Training (CT).G2 (Experimental Group): ALMA.

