Mitigation Strategy and Design Justification: To address these potential sources of bias, the statistical analysis will include prespecified covariates such as age, education level, and baseline MoCA stratum, with additional clinical and psychological variables examined in exploratory or sensitivity analyses. The planned comparison between G2 and G1 will help assess whether the multidimensional and group-based components of ALMA provide added value beyond individual cognitive training. However, because the trial is not designed to isolate each intervention component separately, findings will be interpreted as reflecting the comparative effectiveness of the intervention packages rather than the independent effect of a single component.

Ecological Validity and Experimental Control: The design prioritizes ecological validity by evaluating ALMA as a complex intervention delivered in a realistic oncology-related context. This approach may reduce experimental purity because the intervention combines cognitive stimulation, psychoeducation, professional support, peer interaction, and ecological task practice. Nevertheless, this design is appropriate for evaluating the feasibility and potential clinical relevance of ALMA as an intervention package for women with breast cancer undergoing active treatment.

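### Neither stratification factor is in the primary model; balance of the MoCA stratum is wrongly called guaranteed, and Sections 3.9 and 4.1 disagree on whether that stratum is a covariate

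*Protocol article*

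**What the plan says.** Protocol article, Section 2.5: "Randomization will be stratified based on two baseline prognostic variables". These are baseline MoCA, cut at 26, and treatment modality in two classes, which makes four strata. Within strata, women are "randomly assigned to one of the three study arms using randomly varied blocks of size 3 and 6".

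Section 3.9 sets out a linear mixed model for MoCA with group, time, Group × Time and a random intercept, fitted unadjusted and adjusted. In the adjusted model, "a maximum of two pre-specified baseline covariates will be simultaneously controlled for as fixed effects: chronological age (in years) and educational level" in years of schooling. On the MoCA stratum it says: "Baseline cognitive stratification variables will be excluded from the model as covariates, given that their equilibrium across groups is already mathematically guaranteed". Treatment modality is in a list of further variables that "will be exclusively examined in exploratory or sensitivity analyses rather than included simultaneously in the primary adjusted model".

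Section 4.1, under the mitigation strategy, says: "the statistical analysis will include prespecified covariates such as age, education level, and baseline MoCA stratum".

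**The concern.** Three things need attention.

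1. Sections 3.9 and 4.1 describe the covariates for the same analysis and cannot both be followed. One allows two covariates and rules the MoCA stratum out. The other names three and includes it.
2. The reason given for ruling it out is not true of the randomization in Section 2.5. It would not be a sufficient reason even if it were true.
3. Stratifying on a factor that predicts the outcome makes the arms alike on it and so reduces the real variability of the treatment contrast. A model without the factor leaves its variance in the error term, and the reported standard error does not show the reduction. The trial then pays for stratification without collecting the precision.

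**Working it through.** **Inputs from the article.** 63 women, 1:1:1, 21 per arm (Section 2.4); four strata, blocks of 3 and 6 (Section 2.5); difference 2.95 and SD 3.48 (Section 2.4), where 2.95/3.48 = 0.848 reproduces the stated d of about 0.85. The SD is taken here as the SD of change. The article gives no figure for balance, so there is none to reproduce.

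**Assumed, because the article does not give them.** Prevalence of each stratification factor 30–70%; T0–T1 correlation ρ of 0.6 to 0.8 with equal variances at both visits; the cut at 26 acting as a median split; a modality effect on change of 0 or 1 point with a 50:50 split.

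**Step 1: is balance guaranteed?** A block of 6 that stops part-way can leave two arms 2 women apart in one stratum. Each MoCA level contains two strata, so the gap there can reach 4. In 20,000 simulated allocations per scenario:

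| Result across the three arms | Share of trials |
|---|---|
| MoCA stratum exactly balanced | about 5–6% |
| Gap of 2 or more women within a MoCA level | about 57% |
| Gap of 3 or more | about 12% |
| Share with MoCA <26 differs by more than 10 percentage points | about 2–4% |

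The largest gap seen was 4. Balance is therefore approximate and usually close, but it is not guaranteed. Dropout, expected at about 10%, disturbs it further among women with T1 data.

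**Step 2: cost of omission if the strata predict change.** With equal variances, baseline explains (1 − ρ)/2 of the variance of change. A median split keeps 2/π = 0.637 of that. A 1-point modality effect adds variance 0.25, so it explains 0.25/(3.48² + 0.25) = 0.25/12.36 = 0.020. Under near-balance the reported standard error is too wide by k = 1/√(1 − R²), and the two-sided type I error at nominal 0.05 is about 2[1 − Φ(1.96k)].

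| ρ | R², MoCA stratum only | k | Type I error | R² with 1-point modality effect | k | Type I error |
|---|---|---|---|---|---|---|
| 0.6 | 0.20 × 0.637 = 0.127 | 1.070 | 0.036 | 0.148 | 1.083 | 0.034 |
| 0.7 | 0.15 × 0.637 = 0.096 | 1.051 | 0.039 | 0.116 | 1.063 | 0.037 |
| 0.8 | 0.10 × 0.637 = 0.064 | 1.033 | 0.043 | 0.084 | 1.045 | 0.041 |

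**Step 3: simulation of the G2 versus G0 contrast.** 6,000 trials per setting, complete data, two-sided 0.05 without the Holm step, true difference 2.95 for power. The settings are given as the correlation between baseline and change. For ρ of 0.6 to 0.8 this is √0.20 = 0.45 to √0.10 = 0.32 in size, so 0.3 and 0.5 bracket the range.

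| Baseline–change correlation; modality effect | Type I error without / with factors | Power without / with | Mean SE without / with |
|---|---|---|---|
| 0; 0 | 0.052 / 0.053 | 0.77 / 0.77 | 1.07 / 1.07 |
| 0.3; 1 point | 0.044 / 0.050 | 0.76 / 0.79 | 1.08 / 1.04 |
| 0.5; 1 point | 0.033 / 0.054 | 0.77 / 0.83 | 1.09 / 0.99 |

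**Step 4: how the factors must enter.** In an example REML fit on complete two-visit data, adding the strata as main effects left Group × Time unchanged (1.6768, SE 1.0445 in both fits). Adding strata × time changed the fit (SE 0.955). A main effect shifts both visits equally and cancels from the change.

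**The case against.** The best defence is that Section 3.9 is the operative text, while Section 4.1 is discussion and says only that covariates are such as those named. Section 3.9 also gives a second reason, protection against overfitting with 21 women per arm, which would cover the MoCA stratum as well. Both points carry weight. A reader can tell which section should govern, but Section 4.1 still calls prespecified a covariate that Section 3.9 forbids. Parsimony could be met by choosing the stratification factors as the two covariates.

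Four stronger readings are tempting and are not supported:

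- **Both factors are dropped because balance is guaranteed.** Section 3.9 gives that reason only for the cognitive stratification variables. Treatment modality is left out under the parsimony limit.
- **The result will be biased or falsely positive.** Imbalance is small and the error is in the conservative direction.
- **The conflict lets an analyst choose the answer.** Neither section mentions a stratum × time term. If the stratum enters as a main effect, Group × Time is the same under either section on complete data. A simulation with 10% random dropout (assumed SD 3.5, T0–T1 correlation 0.7, simple allocation) moved the estimate by 0.06 MoCA points on average and the standard error by about 1%.
- **Unequal arm sizes prove the point.** Arms of exactly 21/21/21 arise in about 20% of simulated trials, but that describes total arm size and not balance of the MoCA stratum.

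**Conclusion.** The point holds in a limited form. The contradiction between Sections 3.9 and 4.1 is plain on the page, and the claim of guaranteed balance is incorrect. Neither conclusion depends on an assumption about outcomes. The loss from omitting the factors does: a standard error about 3–8% too wide and a type I error of about 0.03–0.045, for T0–T1 correlations of 0.6 to 0.8, a median split at 26 and a modality effect of 0 to 1 point. If the strata do not predict change, nothing is lost. The article itself gives reason to expect some prediction. It calls both factors prognostic and warns of ceiling effects, and on a 30-point scale a woman starting at 26 or above can gain at most 4 points. This is a worthwhile, nearly free improvement and a correction of wording. It does not threaten the validity of the trial and ranks below a must-fix.

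**What to change.** 1. In Section 3.9, put both stratification factors (MoCA <26 or ≥26, and treatment modality) in the primary model as factor × time terms, or as covariates in a baseline-adjusted model of T1. Main effects alone in the present mixed model would not do. Age and education as now planned have the same limitation.
2. Delete the clause claiming guaranteed balance.
3. Make Sections 3.9 and 4.1 list the same covariates.
4. If the two-covariate limit is to stay, the stratification factors could take the place of age and education. That is a modelling choice for the sponsor.

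Cost: a change of wording. Both factors are recorded before randomization. Two terms use about 2 residual degrees of freedom, for example 52 instead of 57 − 3 = 54 with 57 completers.
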